### Data collection and management

Baseline clinical information (disease severity, global cognitive function, MCI, DAT-SPECT, brain structural MRI, Hoehn and Yahr stage, most affected side, etc.) are collected from the participant’s journals. All other data will be collected on paper forms and/or computer programs. All collected data will be entered into a joint database where each participant is given a study number. The personal identifier for each study number is stored in a locked compartment separated from the study-data. To ensure data quality an independent researcher will re-score 10% of the data.

After including 20 cases in each arm of the study. Interim analyses will be performed on the criteria test and the near transfer test pre and post as well as results during training to ensure data quality.

Results will be reported as scientific reports in peer-reviewed journals and international conferences. Attempts will be made to report back to the community through patient organizations.

#### Data analysis

A statistical plan will be developed before unblinding and data-analysis. The primary data analysis will be performed with an intention-to-treat principle.

Descriptive statistics will be presented by means and standard deviations for normally distributed data, while for variables with non-normal distributions medians and interquartile range will be presented. Frequencies and percentages will be presented for categorical data. Differences between the treatment groups at baseline will be tested using a multivariate analysis of variance.

The effects of the intervention will be assessed with the intention-to-treat principle where continuous outcomes will be analyzed using linear mixed models and categorical outcomes will be analyzed using generalized estimated equations. A random factor will be included for each subject. The fixed factors include treatment (updating or placebo intervention), test sessions (one, two, and three), and an interaction term between the treatment group and test session. If there are baseline factors that differ between the groups, they will be included as covariates with fixed effects in the models. The analysis will be conducted similarly regarding secondary outcomes. To assess if there are any moderating factors for training gains, sub-analyses will be performed with age, gender, disease severity, baseline cognitive function, and disease laterality added to the model in interaction with time. For randomly lost measures imputation based on predictive mean matching will be performed.

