### Objectives

The iPARK trial aims to investigate the effect of a process-based cognitive training program that focuses on WM updating, compared to a low dose short-term memory paradigm, in persons with PD.

The specific research questions asked are:
Can working memory updating training lead to a more responsive frontostriatal system by improving the working memory updating ability in trained tasks?Will there be improvements after training to untrained cognitive tasks (transfer effects)?Will there be improvements in self-perceived everyday cognitive function and psychological health?Will the observed improvements sustain 4 months after training?Are there individual factors moderating the effects of training?

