This study has many strengths. Among them is the inclusion of an active control condition similar to the intervention of interest in all aspects except that the control condition does not include any updating in the training tasks. The majority of intervention studies use a no-contact or waiting list control and if a control-intervention is implemented it is often different from the training intervention, leading to a difference in expectations. To minimize the effect of expectation and to enable blinding, both study arms of the iPARK trial will be presented as equal interventions. Nevertheless, expectations of improvement will be measured before some post-tests to see if the two groups differ in that respect. Thereby, the iPARK trial will be able to answer if it is the updating itself that is causing the improvement. Furthermore, the iPARK trial will establish if there are any moderating factors for improved cognition after training in PD such as baseline cognitive function, age, gender, disease stage, and parkinsonian medication dose. Also, information on training results, motivation, perceived attention during training, time of day for each training session will be analyzed and provide more information as to why some participants improve, and others do not. Apart from measuring transfer to other cognitive tasks, the iPARK trial will also assess changes in psychological health and wellbeing. Finally, very few studies on cognitive training in persons with PD have performed any long term assessment, therefore the four-month assessment included in this study will provide knowledge on the long-term effect of training.

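### As written, the moderator sub-analysis crosses each factor with time and not with treatment, so it can attribute to updating training a difference in gain that is common to both arms

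*Protocol article*

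**What the plan says.** The Objectives section states the aim as a contrast: updating training "compared to a low dose short-term memory paradigm, in persons with PD". Its fifth research question is "Are there individual factors moderating the effects of training".

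The Data analysis section builds a linear mixed model with a random subject factor and fixed effects for treatment, "test sessions (one, two, and three", and "an interaction term between the treatment group and test session". The moderator sentence then gives its purpose, "To assess if there are any moderating factors for training gains", and its method: "sub-analyses will be performed with age, gender, disease severity, baseline cognitive function, and disease laterality added to the model in interaction with time". Treatment is not named in that interaction. The article nowhere gives a factor by treatment by session term, a by-arm analysis, or a restriction to the updating arm.

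The Discussion says that "the iPARK trial will establish if there are any moderating factors for improved cognition after training in PD". Its examples are baseline cognitive function, age, gender, disease stage and parkinsonian medication dose. Medication dose is not in the Data analysis list, although Table 2 collects it (as LEDD) at all three sessions.

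**The concern.** In a two-arm trial, a factor moderates the effect of training if the difference in change between updating and placebo varies with the factor. A factor-by-session term does not contain that difference. It shows whether people with more of the factor change more, whichever program they used.

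The distinction matters in this trial. Every outcome is measured three times, so practice gain is likely in both arms, and the Discussion itself allows that the control program may improve some tested functions. Age and baseline cognition could plausibly predict such gain in either arm. If the sentence is followed literally, such a factor could be published as identifying who benefits from updating training when the benefit is the same for everyone.

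**Working it through.** **The plan's own figure.** The sample size section uses 40 per arm, a difference in change of 2.6 and a pooled SD of 1.94, and states power of 0.9996. The SE of the difference is 1.94 × √(1/40 + 1/40) = 0.434, and 2.6 / 0.434 = 5.99. Two-sided power at 0.05 is 0.99997 by the normal approximation and 0.99996 by the noncentral t. This is slightly above the stated figure, and the gap does not matter here. The figure concerns treatment by session and does not carry over to moderators.

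**What the written term estimates.** Take change from baseline to the first post-test. Let the factor's slope on change be b_U in the updating arm and b_P in the placebo arm. With equal arms and a factor balanced between them:

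- factor × session estimates (b_U + b_P) / 2;
- factor × treatment × session estimates b_U − b_P, which is the moderation.

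The first can be large when the second is zero, and zero when the second is large. This is algebra and depends on no assumed value.

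**No true moderation, common slope.** Inputs: 40 per arm (protocol); change SD of 1, a standardised continuous factor, and slopes b_U = b_P = b (all assumed). The SE of factor × session is 1/√80 = 0.112. Approximate rejection probability is Φ(b/0.112 − 1.96), plus a negligible opposite tail.

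| Common slope b (SD per SD) | b / SE | Normal approximation | Simulated, factor × session | Simulated, three-way |
|---|---|---|---|---|
| 0.1 | 0.89 | 15% | about 14% | about 5% |
| 0.2 | 1.79 | 43% | about 42% | about 5% |
| 0.3 | 2.68 | 77% | about 74% | about 5% |
| 0.4 | 3.58 | 95% | about 93% | about 5% |

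**Moderation in the trained arm only.** Assume b_U = 0.5 and b_P = 0. Factor × session estimates 0.25 with SE 0.112, a ratio of 2.24. The three-way term estimates 0.5 with SE √(1/40 + 1/40) = 0.224, also a ratio of 2.24. Both have power of about 61% by the approximation and about 57% in simulation. The written term loses almost no detection here, but it shows half the true value and cannot be told apart from a slope of 0.25 common to both arms.

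**Opposing slopes.** Assume b_U = 0.25 and b_P = −0.25. The average is zero by construction, so factor × session rejects in about 6% of trials, essentially the alpha level. The three-way term rejects in about 56%. This shows that cancellation is possible, not that it is likely.

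**Price of the correct term.** For a factor split evenly in each arm, on the protocol's scale and reading 1.94 as the SD of change (an assumption):

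- factor × session: SE 0.434; difference detectable with 80% power 2.80 × 0.434 = 1.22 points;
- three-way: SE 1.94 × √(4/20) = 0.868; detectable difference 2.80 × 0.868 = 2.43 points.

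By simulation, the three-way term has about 84% power if the treatment effect differs by 2.6 points between factor levels, and about 31% if it differs by 1.3.

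**The case against.** **The sentence may be shorthand.** The factors are added to a model that already holds treatment by session, the text does not say that they are crossed with time alone, and a statistical plan is promised before unblinding. That plan can settle exact terms, so a reader should not infer that the authors rejected the three-way term or that research question 5 will certainly go unanswered. What stands is that the same paragraph spells out treatment by session for the base model and names only time for the moderators. An analyst following the text would fit the narrower term.

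**Predictors of gain are a fair question.** The moderator sentence speaks of training gains, and the Discussion wants to know why some participants improve and others do not. But research question 5 asks about the effects of training, and the factors enter a model holding both arms. Predictors of gain within the trained arm would need that arm to be separated.

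**The illustrations rest on assumed slopes.** This is correct: the article gives no association between any factor and practice gain. It would go too far to say that every factor predicting practice gain will be declared a moderator, since at a slope of 0.1 that happens in about 14% of trials. Nor does the written term generally miss true moderators; a serious loss of detection needs slopes that oppose each other.

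**The list mismatch is small.** The Discussion offers its list as examples, and disease stage and disease severity plausibly overlap. Only medication dose is promised without a planned analysis.

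**Conclusion.** The point holds as a should-fix. The stated moderator term does not match research question 5, because it averages over the arms when the question concerns the difference between them. The main harm is misattribution. Under assumed common slopes of 0.1 to 0.4 SD and no true moderation, a factor would be reported as a moderator in about 14% to 93% of trials, against about 5% with the three-way term. Those rates depend on the assumed slopes; the mismatch itself does not.

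A reader might infer that the trial's main result is at risk. The document does not support that: the treatment-by-session test, the secondary outcomes, the sample size and the randomisation are untouched. Even with the right term, 40 per arm gives good power only for moderation about as large as the whole assumed treatment effect, so the Discussion's promise to establish moderators is stronger than the design can carry.

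**What to change.** In the Data analysis section, or at the latest in the statistical plan before unblinding:

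1. State that each moderator enters with its main effect, factor × session and factor × treatment, and that moderation is judged on factor × treatment × session. Report that term at the post-test and at the 16-week follow-up, since the model has three sessions and research question 4 concerns persistence.
2. Report factor × session, if at all, as a predictor of change and not as moderation.
3. Add medication dose (LEDD, already collected) to the Data analysis list, or drop it from the Discussion.
4. Describe the moderator analyses as exploratory.

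This needs wording only, with no new data or participants. The downside is precision: for a balanced binary factor the three-way term has about twice the standard error of factor × session (0.868 against 0.434 on the protocol's scale), so fewer moderators will reach significance.

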## Discussion

The iPARK trial is a randomized controlled double-blinded cohort study to assess the efficacy and long term effect of a computer-based training program performed from home in persons with PD. The intervention of interest is a process-based training focusing on working memory updating. The study will investigate if updating training will improve updating function in individuals with PD and if there are any transfer effects to other cognitive domains, self-perceived cognitive function, and quality of life. The study is designed to indicate any potential of a responsive striatal system also in persons with dopamine depletion. The overarching hypothesis is to provide support to that an impaired striatal system can be responsive to a non-invasive, non-pharmacological intervention of working memory updating which in turn can promote cognitive health and brain maintenance, which can contribute to reduced cognitive decline.

Cognitive decline is common in PD and is seriously affecting patients’ everyday life. Recent studies have also shown that PD complicated by cognitive dysfunction confers a shorter life expectance compared to PD with normal cognitive function [52]. The demand for non-pharmacological interventions is increasing and there is, although modest, growing evidence of the benefit of cognitive interventions in PD [20–22, 24]. While some studies have shown the efficacy of cognitive interventions in persons with PD, studies on newly diagnosed patients, excluding those with severe cognitive decline, are sparse.

The iPARK study aims to target patients with mild clinical symptoms of PD (no more than stage 3 on the Hoen and Yahr scale) without dementia. More advanced disease stages constitute other difficulties such as freezing of gate and levodopa-induced dyskinesia. Also, the dopamine depletion is more severe at later stages, which probably makes it harder to be stimulated by nonpharmacological interventions. Therefore, it is more likely that individuals early in the disease will have a more responsive striatal system. Also, a recent meta-analysis from the Cochrane Library found no evidence for any important cognitive improvement after 4 to 8 weeks of cognitive training in PD-MCI and PDD [53]. This indicates that cognitive interventions might be more suitable early in the disease when the cognitive decline is less pronounced.

This study has many strengths. Among them is the inclusion of an active control condition similar to the intervention of interest in all aspects except that the control condition does not include any updating in the training tasks. The majority of intervention studies use a no-contact or waiting list control and if a control-intervention is implemented it is often different from the training intervention, leading to a difference in expectations. To minimize the effect of expectation and to enable blinding, both study arms of the iPARK trial will be presented as equal interventions. Nevertheless, expectations of improvement will be measured before some post-tests to see if the two groups differ in that respect. Thereby, the iPARK trial will be able to answer if it is the updating itself that is causing the improvement. Furthermore, the iPARK trial will establish if there are any moderating factors for improved cognition after training in PD such as baseline cognitive function, age, gender, disease stage, and parkinsonian medication dose. Also, information on training results, motivation, perceived attention during training, time of day for each training session will be analyzed and provide more information as to why some participants improve, and others do not. Apart from measuring transfer to other cognitive tasks, the iPARK trial will also assess changes in psychological health and wellbeing. Finally, very few studies on cognitive training in persons with PD have performed any long term assessment, therefore the four-month assessment included in this study will provide knowledge on the long-term effect of training.

There are also potential limitations of the trial. The training will be unsupervised, which can make it difficult to maintain the motivation needed to complete the training. It can also be difficult to ensure participants are engaging in the training. The pros of an intervention being performed from home are that it can be implemented in everyday clinical practice with relative ease and low cost. To contribute to compliance with the intervention and the planned pre- and post-tests the participants will receive thorough information on what is expected of them during the study period. As a measure of engagement in the task, they will be given questions before and after training on motivation and execution in combination with logged results for each training session. Even though the similarity of the two intervention arms is a considerable strength, it also forms a potential limitation. The control condition could cause improvements in some of the tested functions, as well as psychological health and wellbeing, and thereby mask improvements of the updating training. Some participants might consider the control-condition too easy and drop-out while participants of the updating condition might consider it too hard. It is therefore important to register the reason why participants chose not to follow through with the intervention.

In conclusion, we expect that the iPARK trial will provide novel and clinically useful information about whether updating training is an effective cognitive training intervention for persons with PD. The iPARK trial will contribute to a better understanding of cognitive function in PD and evaluate a new non-pharmacological intervention for PD. If the training is successful, the next stage will be to conduct dopamine-PET and fMRI investigations before and after training as well as kinematic movement registration. Such further measurements will allow for a broader understanding of the effects of working memory updating. Thereby, providing knowledge about underlying mechanisms and answer if a period of updating training can stimulate increases of dopamine transmission also in PD.

## Trial status

The iPARK trial started in January 2017. Recruitment started in February 2017 and will continue until February 2023. The end date for the trial is July 2023. Any changes to the protocol will be made in the trial registry at ClinicalTrials.gov.

## Data Availability

The datasets generated and/or analyzed during the current study are not publicly available due to the ethical Review Act but are available from the corresponding author on reasonable request.

## Abbreviations

LEDD: Levodopa Equivalent Daily Dose
NC: Normal Cognition
PD: Parkinson’s Disease
AD: Alzheimer disease
MCI: Mild Cognitive Impairment
PDD: Parkinson’s Disease Dementia
EF: Executive functions
WM: Working Memory
BOLD: Blood Oxygen Level Dependent
PET: Positron Emission Tomography
UKPDSBB: The United Kingdom Parkinson’s Disease Brain Bank
MMSE: Mini-Mental State Examination
WAIS: Wechsler Adult Intelligent Scale
D-KEFS: Delis-Kaplan Executive Function System
TMT: Trail Making Test
PRMQ: Prospective retrospective memory questionnaire
HAD: Hospital Anxiety Depression
SF-36: Short form health survey
KSQ: Karolinska Sleep Questionnaire
UPPS: Urgency, Premeditation, Perseverance, and Sensation Seeking
BART: Balloon Analogue Risk-taking Task
PDQ-39: Parkinsonson’s Disease Questionaire
CIS: Checklist Individual Strength
UPDRS: Unified Parkinson’s Disease Rating Scale
